**Methods/Design:**

An observational population-based study has been designed involving 260 adults newly-diagnosed with colorectal cancer between January 2010 and September 2011 and who were in paid employment at the time they were diagnosed. These cancer cases will be compared to a nationally representative comparison group of 520 adults with no history of cancer from the general population. Eligible cases will have a histologically confirmed diagnosis of colorectal cancer and will be identified through the Queensland Cancer Registry. Data on the comparison group will be drawn from the Household, Income and Labour Dynamics in Australia (HILDA) Survey. Data collection for the cancer group will occur at 6 and 12 months after diagnosis, with work questions also asked about the time of diagnosis, while retrospective data on the comparison group will be come from HILDA Waves 2009 and 2010. Using validated instruments administered via telephone and postal surveys, data will be collected on socio-demographic factors, work status and circumstances, and health-related quality of life (HRQoL) for both groups while the cases will have additional data collected on cancer treatment and symptoms, work productivity and cancer-related HRQoL. Primary outcomes include change in work participation at 12 months, time to work re-entry, work limitations and change in HRQoL status.

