### Sample size

Based on cancer incidence [16] and labour figures [17] it is anticipated that at least 522 working persons with colorectal cancer will be eligible annually. Sample size calculations were based on the number required to detect a 15% difference in work participation between workers with and without cancer assuming a 5% significance level and 80% power. Based on our past experience of recruiting colorectal cancer patients through the QCR and allowing for 85% doctors consent, 70% participant consent, 90% baseline interview completions and 75% retention at 12 months post-diagnosis, we will require initial contact with 258 patients with colorectal cancer to retain 125 patients at 12 months. The wave-on-wave attrition rates among continuing HILDA respondents have been consistently low, approximately 5% each year [18]. Data for 2,590 employed persons enrolled in HILDA aged 45-64 years Australia-wide will be available. HILDA data will be randomly matched 2:1 to patients with colorectal cancer, by gender and 5-year age category. Thus the total sample size to be selected for the study will be approximately 780.

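### Drawing about 520 comparators from up to 2,590 existing HILDA records is an avoidable loss of precision, although the stated 80% power is still essentially met

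*Protocol article*

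**What the plan says.** The comparison group comes from secondary data, HILDA Waves 9 and 10 (Study participants; Data collection sources). On the size of the pool, the Sample size section states: "Data for 2,590 employed persons enrolled in HILDA aged 45-64 years Australia-wide will be available". On how it is used: "HILDA data will be randomly matched 2:1 to patients with colorectal cancer, by gender and 5-year age category". The section ends: "Thus the total sample size to be selected for the study will be approximately 780". The abstract describes 260 patients and a "nationally representative comparison group of 520 adults with no history of cancer".

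The sample size is set to "detect a 15% difference in work participation between workers with and without cancer", "assuming a 5% significance level and 80% power". No proportion is given for either group. The recruitment statement is "we will require initial contact with 258 patients with colorectal cancer to retain 125 patients at 12 months", allowing for "85% doctors consent, 70% participant consent, 90% baseline interview completions and 75% retention at 12 months post-diagnosis".

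The Analyses section restricts comparators to those who responded at both waves. It plans separate multivariable logistic regressions in the cancer and comparison groups, and puts gender in every model with tests for gender interactions.

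**The concern.** Patients are costly to recruit, whereas the HILDA records already exist. Sampling error in the comparison group is therefore the part of the variance that can be reduced without recruiting anyone. Random selection of 520 leaves about 80% of the stated pool unused, and the protocol gives no reason for it.

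The basis of the ratio is also unclear. The 520 is twice 260, and 260 matches the 258 patients to be contacted rather than the 125 to be analysed. Balance on age and gender, which the matching is meant to secure, would then hold for the analysed patients only if consent and retention do not vary by age or gender. A reader also cannot tell whether 2:1 is meant to hold in the analysis, and that changes the power.

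**Working it through.** **Inputs from the protocol.** Significance level 5%; difference 15%, read as percentage points; 258 contacted; 125 retained; rates 0.85, 0.70, 0.90 and 0.75; pool 2,590; HILDA attrition about 5% per wave; 520 comparators; total about 780.

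**Assumptions.** Two-sided test; comparator proportion 35-42.5% as the main range, with 5-20% shown as well; independent observations unless stated.

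**1. The plan's own figures.**
- Total: 260 + 2 × 260 = 780, which reproduces.
- Retention: 258 × 0.85 × 0.70 × 0.90 × 0.75 = 258 × 0.4016 = 103.6, about 104 rather than 125. Retaining 125 needs 125 / 0.4016 = 311.2, so 312 contacts. Both 125 and 104 are carried forward.
- The 125 cannot be checked uniquely without a base rate, but it is attainable: 31% v 16% at 1:1 needs 125 per group, and 50% v 35% at 2:1 needs 126 patients.

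**2. Records left unused.** 2,590 − 520 = 2,070, or 80%. This is an upper bound, because 2,590 is not stated to be net of people with a cancer history or of those missing a wave. After 5% attrition the pool is 2,590 × 0.95, about 2,460. If the 520 are drawn before attrition, 520 × 0.95 = 494 remain.

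**3. Analysed ratio.** 520 / 125 = 4.2 and 520 / 104 = 5.0. If all 520 are analysed, the ratio is 4-5:1, not 2:1.

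**4. Power.** With d = 0.15, patient proportion p1 = p0 + 0.15 and p̄ the size-weighted mean of p1 and p0:

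power = Φ{(d − 1.96·SE0) / SE1}, where SE0 = √[p̄(1 − p̄)(1/n1 + 1/n0)] and SE1 = √[p1(1 − p1)/n1 + p0(1 − p0)/n0].

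| Patients v comparators | p0 = 10% | p0 = 20% | p0 = 35% | p0 = 42.5% |
|---|---|---|---|---|
| 125 v 520 | 98.1% | 93.0% | 86.9% | 85.8% |
| 125 v 2,460 | 99.2% | 96.2% | 91.9% | 91.1% |
| 104 v 520 | 96.5% | 89.3% | 81.6% | 80.3% |
| 104 v 494 | 96.3% | 89.0% | 81.3% | 79.9% |
| 104 v 1,230 | 97.8% | 92.2% | 85.5% | 84.3% |
| 104 v 2,460 | 98.2% | 93.2% | 86.9% | 85.7% |
| 104 v 208 | 91.8% | 81.2% | 72.1% | 70.8% |

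The 1,230 row assumes that weighting and household clustering halve the effective number of comparators. The 208 row applies only if 2:1 is kept among analysed patients.

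With 104 patients, going from 520 to 2,460 adds about 5 points at 35-42.5%, about 4 at 20% and about 2 at 10%. At 5% it adds 0.6 points (99.0% to 99.6%).

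**5. Standard error of the between-group difference.** This is proportional to √(1/n1 + 1/n0). For 125 patients it falls from 0.0996 to 0.0917, or 8%. For 104 it falls from 0.1074 to 0.1001, or 7%.

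**6. Comparison-group regression.** Precision depends on n0 alone: 1 − √(520 / 2,460) = 0.54, so standard errors are up to about 54% smaller.

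**The case against.** A 2:1 matched sample of 520 is a conventional design and contradicts nothing in the protocol. A reader might infer that it loses power the study needs. That does not follow. The only restriction stated for comparators is response at both waves, and nothing says they are dropped when a patient is lost. With all 520 analysed, power is 80-82% even with 104 patients, or 79.9% at worst if 520 shrink to 494. Basing the 520 on contacts increases the number of comparators per analysed patient, so for power it helps. This objection stands, and the point is limited to precision.

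A reader might also infer that most matched comparators belong to patients who never supply 12-month data. That assumes individual linkage. The wording fits category matching at least as well, the planned models are not conditional ones, and the Study design section speaks of matching enrolled participants. That the ratio was set on contacts is itself inferred from the 258, 260 and 520. The plan also keeps gender in all models, compares baseline characteristics and allows weighting for non-completion. Imbalance on age or gender is thus a possibility, not an established defect.

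Finally, patients are the scarce group. Even with unlimited comparators, power at a 42.5% comparator rate is capped at 92.4% with 125 patients and 87.2% with 104. Extra comparators do nothing for time to work re-entry, work limitations or change in HRQoL within the cancer group. This too stands.

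None of this gives a reason to leave free records unused. The gain remains in the between-group comparison and is larger in the comparison-group model.

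**Conclusion.** The plan gives up precision that it could have without recruitment. For the between-group comparison the loss is modest: about 5 points of power at assumed comparator rates of 35-42.5%, and less at lower rates. If weighting and clustering halve the effective comparators, power with 104 patients is still 84-86%, against 80-82% as planned. The larger loss is in the comparison-group regression, where the 54% is an upper figure because the eligible pool may be smaller than 2,460.

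The 80% target is not missed on the natural reading that all 520 are analysed. Only if 2:1 were kept among analysed patients (104 v 208) would power drop to 71-72% at those rates, and the documents do not state that reading. They should exclude it. Using the full pool would also about offset the retention shortfall for the between-group comparison (104 v 2,460 gives 85.7%; 125 v 520 gives 85.8%, both at 42.5%), but not for the cancer-only analyses.

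These figures rest on a two-sided test, a 15-percentage-point difference and comparator rates that the protocol does not supply.

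**What to change.** - Use every HILDA worker aged 45-64 who responded at both waves and has no cancer history.
- Standardise or adjust to the 5-year-age by gender distribution of the analysed cancer patients, with standard errors clustered on household.
- If a matched sample is kept for presentation, match it to the analysed patients and say so.
- State the number of eligible comparators after both exclusions, and restate power for analysed patients with the assumed comparator proportion. Put 258, 125, 260, 520 and 780 on one basis.

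The cost is in analysis only: a weighted or stratum-adjusted comparison replaces a simple matched one. No further data collection or recruitment is needed.

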### Recruitment

As mandated by QCR protocols, patients' names and the names of their doctors will be accessed via the QCR and initial letters sent to each patient's doctor requesting permission for the patient to be approached, followed by reminder letters and telephone calls if necessary. All patients for whom doctor's consent is obtained will be mailed a study invitation letter, an information sheet and consent form. Three weeks after the initial patient letter, non-responders will be telephoned to gauge their interest in the study and screened for their eligibility.

### Data collection sources

Data will be collected during this project from four sources (Table 1):

**Table 1 T1:** Questionnaire item domains at each time point by cancer cases and general-population comparison group

	Cancer Group		Comparison Group
**Method**	**Telephone interview**	**Mailed questionnaire**	**Face-to-face interview**

Time 1^a^	1. Socio-demographics^b^ 2. Cancer treatments 3. Symptoms (MSAS^b^) 4. Work questions^a^ 5. Work limitations (WLQ)	6. Quality of life (SF-36)^b^ 7. Health behaviours & conditions^b^ 8. Cancer-specific quality of life (FACT-C) 9. Financial strain^b^	Question groups 1, 4, 6, 7, 8, 9 from HILDA Wave 9, 2009 data

Time 2	Repeat question groups 2-8		Question groups 1, 4, 6, 7, 8 from HILDA Wave 10, 2010 data

^a ^Time 1 for the Cancer Group occurs six-months after diagnosis however retrospective work questions are asked about their time of diagnosis (baseline) and about their current time (six months after diagnosis) therefore a common one year period will be compared across the cancer and comparison groups for key work questions.

^b^These questions are the same as those in the comparison group to enable direct comparison between groups.

Abbrevs: FACT-C = Functional Assessment in Cancer Therapy plus Colorectal Cancer module, HILDA = Household, Income and Labour Dynamics in Australia, MSAS = Memorial Symptom Assessment Scale, SF-36 = Medical Outcomes Study Short Form 36, WLQ = Work Limitations Questionnaire.

#### 1) Pathology reports held within the QCR (cancer group)

Clinical data will be collected including tumour site, histopathological tumour type, degree of differentiation/grade, degree of metastasis and stage of disease (e.g, TNM or Dukes staging).

#### 2) Telephone interviews (cancer group)

Participants with cancer will take part in structured telephone interviews at 6 and 12 months after diagnosis. At the 6-month data collection time point we will also ask participants to recall work-related information at the time they were diagnosed with cancer (baseline). Telephone interviews will be undertaken in order to maximise response rates, reach a wide geographical region and minimise participant burden, the latter being important in a working population that may require out-of-hours contact. Interviews will be conducted by trained and experienced interviewers. To minimise respondent burden, interviews will be kept to approximately 30 minutes each. A flexible interview schedule will be adopted and tailored to suit the schedules of working participants.

#### 3) Self-administered mailed questionnaire (cancer group)

To supplement the data collected from the telephone interview, and to address items of a more sensitive nature (e.g., financial strain, health behaviours), additional postal surveys will be sent to participants with cancer immediately after the telephone interview. The surveys will take approximately 20 minutes to complete.

#### 4) General-population (comparison group) survey data

Secondary data from HILDA survey waves 9 and 10 (2009 and 2010 data) will be used to assess the comparison group. These data are collected by face-to-face interviews.

### Specific questionnaire items and measures

*Generic baseline socio-demographic information*for the cancer and comparison groups will include items on age, gender, education level, country of birth, culture, marital status, household income, health and other insurances, postcode of residence, number and age of children.

*Participants' work situations, generic HRQoL, health behaviours and conditions*will be collected at both time-points (Table 1) with identical items for the cancer and comparison groups. Work situation items include a compilation of validated tools from Australian government surveys (eg Australian Bureau of Statistics (ABS) Labour Force Survey, ABS 1999 Survey of Living Standards) and ask about: employment status, usual and preferred weekly hours, reasons for working part time, occupation, occupation change, industry, trade union membership, paid sick leave, paid holiday leave, expected resignation or dismissal, supervisory responsibilities, employer type, workplace size, job satisfaction, if the respondent has a disability, type of disability, disability commenced in the last year, impact of disability on work probability, financial strain (e.g., access to emergency funds, bills paid late), intended age of retirement and intentions of stopping work during next three years. Generic HRQoL will be evaluated using the widely-used and validated Medical Outcomes Survey Short Form (SF-36). Physical activity estimates will be obtained via the International Physical Activity Questionnaire (short-form) [19]. Other standard health behaviours and conditions (smoking, alcohol consumption, height, weight and chronic illnesses) will also be asked.

*Cancer treatments, symptoms, cancer-specific HRQoL and work limitation items*will be collected at both time-points for participants in the cancer group (Table 1). The Memorial Symptom Assessment Scale (MSAS) will be used as our measure of prevalence and severity of common cancer treatment and disease symptoms [20]. This instrument has proven validity and reliability among a sample comprising persons with prostate, breast, colon and ovarian cancers [20]. Cancer-specific HRQoL will be assessed using the Functional Assessment of Cancer Therapy general questionnaire (FACT-G) plus the colorectal cancer module; (FACT-C). The FACT-G (Version 4) is a 36-item questionnaire with four subscales: physical; social; emotional; and functional well-being. The FACT-C has demonstrated validity and reliability, is brief and sensitive to changes in functional status [21]. In addition, Queensland general-population norms are available to use for comparisons [22]. The 25-item Work Limitations Questionnaire (WLQ) will be used to assess potential difficulties experienced at work [23]. The WLQ covers four dimensions; time management, physical demands of work, mental-interpersonal demands (cognitive job tasks, on-the-job social interactions) and output demands (diminished work quantity and quality). The WLQ has strong psychometric properties and has tested in patients with various chronic diseases [23].

### Analyses

All analyses will include gender as a factor and will test for interactions of gender with other factors in the model. Gender differences are important, as not only do men and women have different work participation rates, work hours and occupation types in the general population [17], they respond and adjust differently to illnesses, have different health behaviours and other risk factors for cancer [24]. Where no effect modification is observed, pooled results will be presented. Socio-demographic characteristics will be compared at baseline to identify any statistically significant differences between the cancer and comparison groups. Descriptive analyses will be conducted to chart employment transitions over the year since diagnosis among the cancer group and over 2009-2010 year period among the comparison group. Although the first time point for the cancer group is six months after diagnosis, participants are asked to recall work circumstances (occupation type, hours worked, industry etc) at the time of diagnosis (retrospectively) and at time 1 (six months after diagnosis). Separate multivariable logistic regression modelling will identify explanatory variables that are significantly associated with work participation in the cancer and comparison groups. For these models, adjusted odds ratios with 95% confidence intervals and p-values will be computed. Cox proportional hazards models will assess time to work resumption in the participants with cancer and significant correlates of timely work re-entry. Mixed-effects modelling for the cancer group will be used to examine change in HRQoL scores (time 1 - time 2) by participants who reduce or leave in that time versus those who do not. We will also compare HRQoL scores between the cancer and comparison groups at time 2. Data on work limitations measured in the cancer group will be scored across the four domains and mixed-effects modelling undertaken to assess changes in scores between time 1 and time 2. Reasons for study withdrawal in the cancer sample will be closely monitored. Descriptive analyses of baseline variables for the 'completers' and 'non-completers' will identify any possible bias and the source and, if necessary, subsequent analyses will be weighted accordingly. In the comparison group, only responders at both HILDA Waves 9 and 10 will be included.

We expect the relationship between work participation and HRQoL to be complex and therefore, to complement the analyses above, statistical modelling will be undertaken to allow for health status to be an endogenous component of work participation. We will address this using the estimation of two-stage simultaneous probit least squares [25]. Unlike previous analyses examining the relationship between health status and work participation [25,26] in patients with chronic illness, we will have comprehensive clinical data to describe disease status in addition to self-reported health status. STATA SE (Version 11.0) will be used for all analyses. Written reports of the study findings will adhere to the STROBE (Strengthening the Reporting of Observational studies in Epidemiology) statement for quality purposes.

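### Beyond matching on gender and 5-year age, a baseline significance comparison is the only stated handling of cancer-versus-comparison differences, and no stated analysis names an adjusted between-group contrast

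*Protocol article*

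**What the plan says.** All of this is in the Methods of the protocol article.

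- **Matching (Sample size):** "HILDA data will be randomly matched 2:1 to patients with colorectal cancer, by gender and 5-year age category". No other matching factor is given.
- **Baseline comparison (Analyses):** "Socio-demographic characteristics will be compared at baseline to identify any statistically significant differences between the cancer and comparison groups". The section does not say how the result will be used.
- **HRQoL between groups (Analyses):** "We will also compare HRQoL scores between the cancer and comparison groups at time 2". No method or covariate is attached to this sentence.
- **General rule (Analyses):** "All analyses will include gender as a factor and will test for interactions of gender with other factors in the model". Gender therefore enters the HRQoL comparison too.
- **Work participation (Analyses):** "Separate multivariable logistic regression modelling will identify explanatory variables that are significantly associated with work participation in the cancer and comparison groups".
- **Other models (Analyses):** the Cox model and the mixed-effects models are for the cancer group. The possible weighting concerns completers versus non-completers. The two-stage probit and least-squares model is there because health and work influence each other.

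Under Specific questionnaire items and measures, socio-demographic items are collected in both groups, and the work items are identical in the two groups. Table 1 marks the socio-demographic questions as the same in both, and work circumstances at diagnosis are recalled by the cases.

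**The concern.** The comparison group is what the article offers over earlier work: its Background faults a previous Australian cohort for having none, so that work cessation could not be attributed to cancer. Hypothesis 1 (work change more than 15% higher in cases) and Aim 4 (HRQoL at time 2) both rest on the cancer-versus-comparison contrast.

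That contrast is not randomised. Cases are Queensland residents who pass through doctor consent and participant consent. Comparators are members of a national household panel who responded at both waves. Differences in education, occupation and household are to be expected, and the Background itself lists education, marriage, occupation type and physically demanding work among factors linked with delayed return to work or stopping work.

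Whether a factor confounds depends on how unbalanced it is and how strongly it affects the outcome. A p-value mixes the imbalance with the sample size and carries no information on the effect. If the stated text were followed and nothing added, imbalance in these factors could be read as an effect of cancer.

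**Working it through.** **1. The plan's own numbers.** The Sample size section contacts 258 cases to retain 125. Its four rates multiply to 0.85 × 0.70 × 0.90 × 0.75 = 0.4016, and 258 × 0.4016 = 103.6, so 125 is not reproduced; retaining 125 needs 125 / 0.4016 = 311.2, that is 312 contacts. The 125 itself fits a two-sided 5% test with 80% power and 2:1 allocation at an assumed 33% v 48% (n = 124) or 35% v 50% (n = 126). The shortfall is a separate problem. It matters here only because it leaves several candidate sizes for the baseline comparison:

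- 125 v 250: planned number at 12 months, 2:1.
- 104 v 208: what the stated rates deliver at 12 months.
- 138 v 276: first interview, 258 × 0.85 × 0.70 × 0.90 = 138.2.
- 138 v 520: the same cases, if all 520 comparators are used.
- 260 v 520: the abstract.

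**2. How often a 10-point imbalance would be missed.** Two-sided test at 5% (the article does not state sidedness), with the characteristic 10 points more common in cases. Prevalences are assumed. With P the pooled proportion,

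SE0 = √[P(1−P)(1/n1 + 1/n2)], SE1 = √[p1(1−p1)/n1 + p2(1−p2)/n2], power ≈ Φ[(0.10 − 1.96·SE0)/SE1].

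Example, 125 v 250 with 40% v 30%: P = 0.3333, SE0 = 0.0516, SE1 = 0.0525, power = Φ(−0.023) = 0.491, so 51% are missed. Same prevalences at 260 v 520: SE0 = 0.0358, SE1 = 0.0364, power = Φ(0.819) = 0.794, so 21% are missed.

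| Cases v comparators | Missed, comparator 20% | 30% | 40% |
|---|---|---|---|
| 104 v 208 | 50% | 58% | 61% |
| 125 v 250 | 42% | 51% | 55% |
| 138 v 276 | 38% | 47% | 51% |
| 138 v 520 | 30% | 39% | 44% |
| 260 v 520 | 13% | 21% | 24% |

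At a comparator prevalence of 10%, 125 v 250 misses about 25%.

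**3. What is left in an unadjusted work contrast (illustration, sizes assumed).** For independent binary factors with additive effects, the shift is the sum of imbalance × effect on outcome risk.

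- Three factors, each 10 points more common in cases and each raising risk by 15 points: 3 × 0.10 × 0.15 = 0.045, or 4.5 points. Against the 15-point target this is 4.5 / 15 = 30%.
- With the simulated standard error of 0.0505 at 125 v 250 and no true cancer effect, 0.045 / 0.0505 = 0.89, and Φ(−1.96 + 0.89) + Φ(−1.96 − 0.89) ≈ 0.14. The unadjusted contrast would be significant in about 14% of studies instead of 5%.
- Three factors with 5-point imbalances and 10-point effects: 3 × 0.05 × 0.10 = 0.015, or 1.5 points, with about 6% false positives by the same formula.
- If one of the three larger factors runs the other way: (2 − 1) × 0.10 × 0.15 = 1.5 points.

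In the simulation of the first case, adjusting for all three factors regardless of p-value removed the shift (mean 0.000), and the standard error was 0.0494 instead of 0.0505.

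**4. HRQoL.** The documents give no figure for how strongly these factors affect SF-36 scores. By the same product, one factor with a 10-point imbalance and an assumed effect of 5 or 10 SF-36 points would shift the comparison by 0.5 or 1.0 points.

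**The case against.** The strongest reply is that much of this is silence in a condensed article, and covariate lists are commonly left to a full analysis plan. The baseline sentence can be read as no more than a descriptive table. This stands in part, and it rules out three stronger readings.

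- A reader might infer that covariates will be selected by the baseline test, or that non-significance will be taken as balance. The article says neither. A figure for the bias left after p-value screening would describe a procedure the authors did not write, so none is used here.
- A reader might infer that the time-2 HRQoL comparison is unadjusted. The sentence only names no covariate, and gender applies to every analysis.
- A reader might take it as general that the test misses half of such imbalances. That depends on sample size and prevalence: it fails at 260 v 520 and for rarer characteristics.

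The confounder sizes in the illustration are also assumed, all act in one direction, and concern work rather than HRQoL.

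The reply does not remove the point. The article does name a criterion, statistical significance, and it is a poor one for this purpose. It also specifies the work models as separate by group, and these cannot yield an adjusted between-group estimate whatever covariates they contain.

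**Conclusion.** The point holds in limited form. Apart from matching on two factors and a gender term, the only stated handling of cancer-versus-comparison differences is a significance comparison with no stated consequence, and none of the stated models is described as giving a confounder-adjusted contrast between the groups.

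For characteristics of mid-range prevalence (comparators 20-40%, assumed), that comparison would overlook a 10-point imbalance about 42-55% of the time at 125 v 250 and about 13-24% at 260 v 520. The possible distortion of the work contrast is 4.5 points under the larger set of assumptions and 1.5 points under the smaller or partly opposing ones. A larger sample reduces the chance of missing an imbalance but does not reduce the bias in a contrast left unadjusted.

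This is a correction the authors should make because it is nearly free and protects the study's central comparison. It does not show that the results will be wrong.

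**What to change.** - Drop statistical significance as the criterion for baseline differences and describe them as standardised differences.
- State that the time-2 HRQoL comparison, and any between-group estimate of work change, will come from a model with group as a term, adjusted for a fixed set whatever the p-values: age in years, gender, education, country of birth, partner and children, and occupation and usual hours at diagnosis (cases) or Wave 9 (comparators).
- Leave out items that cancer may already have changed by month six, such as current household income, because the cases' first interview is six months after diagnosis.
- Keep the separate logistic models for identifying factors within each group, and say that they do not supply the between-group contrast.

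The cost is a change of analysis wording and a few degrees of freedom. The items are already collected in both groups.
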